### Trial objectives

2.1

*Primary objective:* To assess the association between VET and Anti-Xa in critically ill patients with and without sepsis receiving UFH or LMWH, and to evaluate whether VET can serve as a surrogate for Anti-Xa as the reference assay.

*Secondary objective:* To determine whether VET provides complementary or superior information to Anti-Xa activity for characterizing global haemostatic function, as assessed TGA variables, in critically ill patients with and without sepsis.

*Exploratory objective:* To investigate whether extended VET variables and advanced haemostatic biomarkers provide additional information on anticoagulant effects, to explore dose-exposure-response relationships between drug dose, Anti-Xa, VET, and TGA, to assess the influence of patient-level modifiers, and to generate preliminary signals on the predictive value of laboratory profiles for bleeding and thrombotic complications in critically ill patients with and without sepsis.

Given the observational design and sample size, this study is primarily hypothesis-generating. Clinical events, bleeding and thrombosis, are assessed exploratorily and will be interpreted descriptively without claims of definitive prognostic performance.

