1) Variable: Additional VET variables (CFT, A5, A10, MCF, *α*-angle, lysis time, and lysis index).Metric: Spearman correlations with Anti-Xa and TGA variables; multivariable mixed-effects regression to account for repeated measures.Aggregation: Correlation coefficients (*r*) with 95% CI; regression *β* with 95% CI.Time point: As in primary outcome.Clinical relevance: Explores whether extended VET variables provide complementary or superior information to CT for characterizing anticoagulant effect.2) Variable: Advanced haemostatic biomarkers (PF1 + 2, TAT, PAP, PAI-1, TFPI, FVIII, FXIII).Metric: Correlation with Anti-Xa, VET, and TGA; exploratory path analyses of marker interrelations.Aggregation: Correlation coefficients with 95% CI; descriptive effect-size comparison.Time point: Parallel to VET and TGA sampling.Clinical relevance: Identifies mechanistic markers that may explain discordance between concentration-based assays (Anti-Xa) and functional assays (VET/TGA).3) Variable: Dose-exposure-response relationships (applied dose, Anti-Xa levels, VET, and TGA).Metric: Linear and nonlinear regression models linking administered anticoagulant dose to laboratory readouts.Aggregation: Regression coefficients (*β*) with 95% CI; model fit indices (*R*^2^, AIC).Time point: At all scheduled samplings, stratified by regimen type.Clinical relevance: Assesses whether dosing strategies achieve expected anticoagulant activity defined as Anti-Xa activity within the intended target range regarding dosage and whether functional assays reveal discrepancies not captured by Anti-Xa.4) Variable: Patient-level modifiers (e.g., sepsis status, SOFA score, renal function, albumin, BMI).Metric: Interaction terms in regression/mixed-effects models; subgroup analyses.Aggregation: *β* coefficients for interaction effects with 95% CI; stratified correlation estimates.Time point: As in primary outcome, stratified by clinical subgroup.Clinical relevance: Determines whether specific patient factors systematically influence anticoagulant effect or modify the correlation between Anti-Xa, VET, and TGA.5) Variable: Clinical complications (bleeding and thrombotic events within 24 h).Metric: Exploratory descriptive analysis of concordance between laboratory profiles and event occurrence; logistic regression if case numbers allow.Aggregation: Odds ratios with 95% CI (if feasible); otherwise descriptive frequencies.Time point: Event assessment in the 24 h prior to or following each sampling.Clinical relevance: Provides preliminary signal on the clinical predictive value of Anti-Xa, VET, and TGA in identifying patients at bleeding or thrombotic risk.

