
Specialized haemostasis markers are included to mechanistically characterise discordant profiles between concentration-based heparin activity (Anti-Xa) and functional assays (VET/TGA): PF1 + 2 and TAT as thrombin generation/consumption markers; TFPI as a heparin-responsive anticoagulant pathway marker; PAP and PAI-1 as fibrinolysis activity/inhibition markers. These variables will be analysed descriptively and in focused secondary models to reduce data-driven inference. Table 1 provides an overview about the obtained data.

**Table 1 tab1:** Collected study variables.

Grouping	Variables
Demographic data	Date of ICU admission; Admission diagnosis; Main diagnosis; Gender; Date of birth; Age; Height; Weight; Date of blood collection
Comorbidities	Trauma; Injury Severity Score; Diabetes; Obesity; Coronary heart disease; Chronic arrhythmia; COPD; Other lung diseases; Venous thrombosis; Nicotine abuse; Active tumour disease; Chronic renal insufficiency; Chronic dialysis; Bleeding disorder upon admission; Thromboembolic complication upon admission; Ischemic stroke; Haemorrhagic stroke; Nosocomial infection; Liver diseases
Condition at time of blood collection	Ventilation status; Glasgow Coma Scale; SpO₂; PaO₂; FiO₂; Systolic blood pressure; Diastolic blood pressure; Mean arterial pressure; Heart rate; Catecholamine use and dosage; Inotrope use and dosage; Temperature; Spontaneous respiratory rate; ECMO status; Date of ECMO initiation
Complications within last 24 h	Bleeding (date, volume, transfusion requirements: RBC, FFP, platelets, PPSB, other blood products); Thrombosis; Pulmonary embolism
Severity scores	SOFA; SAPS II
Medication	Sedation and dosage; Platelet aggregation inhibition and dosage; Oral anticoagulation (drug, dosage, time of last intake); Other anticoagulants and dosage; UFH dosage; LMWH dosage and drug name; Parenteral nutrition; Immunosuppressants
Viscoelastic testing (ClotPro®)	LMWH: EX, RVV, ECA, RVH; UFH: EX, RVV, ECA, RVH, IN, HI; Recorded variables: CT, CFT, A5, A10, MCF, Lysis time, Alpha angle
Standard laboratory tests (SLT)	Haemoglobin; Hematocrit; Platelet count; Leukocytes; Prothrombin time (Quick); aPTT; Anti-Xa; dTT; Antithrombin; D-dimer; Fibrinogen; Calcium; Factor VIII; Factor XIII; C-reactive protein; Procalcitonin; Creatinine; Glomerular filtration rate; Urea; ALAT; ASAT; Bilirubin; Albumin; Triglycerides
Advanced haemostatic assays	TAT; PF1 + 2; TGA; PAP; PAI; TFPI

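### Exploratory outcome 5 does not separate events before sampling from events after it, yet reads any odds ratio as predictive; Table 1 lists only the look-back events

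*Protocol article*

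**What the plan says.** Section 2.10 of the protocol article, exploratory outcome 5, names the variable as "Clinical complications (bleeding and thrombotic events within 24 h", with no direction fixed in the name. The time point supplies both directions: "Event assessment in the 24 h prior to or following each sampling". The metric is "Exploratory descriptive analysis of concordance between laboratory profiles and event occurrence; logistic regression if case numbers allow", and the results are to be given as "Odds ratios with 95% CI (if feasible); otherwise descriptive frequencies". The stated relevance is "Provides preliminary signal on the clinical predictive value of Anti-Xa, VET, and TGA in identifying patients at bleeding or thrombotic risk". The exploratory objective in section 2.1 uses the same idea: "to generate preliminary signals on the predictive value of laboratory profiles for bleeding and thrombotic complications".

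Table 1, in the same section, has one group for events, headed "Complications within last 24 h". Its entries are "Bleeding (date, volume, transfusion requirements: RBC, FFP, platelets, PPSB, other blood products); Thrombosis; Pulmonary embolism". A date is listed for bleeding only, and no clock time for any event. No group covers the period after sampling.

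Section 2.2 places the second sample 24 to 72 h after the first. Section 2.16 makes logistic regression conditional on event numbers and calls these analyses hypothesis-generating. Section 2.1 says that events will be interpreted descriptively, with no definitive prognostic claim.

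**The concern.** A laboratory value can predict only what happens after it is measured. For an event in the 24 h before the sample the order is reversed. Bleeding consumes factors and may lead to transfusion (Table 1 itself collects red cells, plasma, platelets and prothrombin complex alongside bleeding). Either kind of event may also lead to a change in anticoagulation. Each of these can move Anti-Xa, clotting time or thrombin generation before the tube is drawn, so the value is then partly a consequence of the event. If such events enter the outcome of a logistic model, the odds ratio mixes prediction with reaction, and the mixture can be weaker than the forward association or point the other way.

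The second problem is capture. The outcome needs events after each sample, but the listed data look backwards. If collection follows Table 1, the part of the window that bears on prediction is largely unrecorded. What is at stake is whether this outcome can deliver even the modest signal it is meant to give.

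**Working it through.** The document gives no event rate, event count, odds ratio or power for this outcome, so there is no figure of the plan's own to reproduce. Three checks were made.

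**1. The two places side by side (section 2.10)**

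| Period | Outcome 5 | Table 1 |
|---|---|---|
| 24 h before each sample | included | listed |
| 24 h after each sample | included | not listed |

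No section says that the two periods are analysed apart.

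**2. How much of the forward window the look-back reaches**

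Let g be the gap between samples in hours, 24 ≤ g ≤ 72 (section 2.2). The look-back at sample 2 spans hours g − 24 to g after sample 1. The forward window of sample 1 spans hours 0 to 24. The overlap is max(0, 48 − g).

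- g = 24: 24 h, full coverage.
- g = 36: 12 h.
- g ≥ 48: 0 h.

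If gaps were uniform over 24 to 72 h (an assumption), the mean overlap is the integral of (48 − g) from 24 to 48, divided by 48: 288 / 48 = 6 h of 24. The 24 h after sample 2 contribute nothing. Each patient has 2 × 24 = 48 forward hours, so the listed data would cover 6 / 48 = 12.5% of them.

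**3. What mixing the periods can do to an odds ratio (illustration with assumed inputs only)**

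First simulation, 300,000 records per row. Before any event, Anti-Xa is standard normal. Event risk follows a logistic model with intercept −3 and a true odds ratio of 1.8 per SD. A prior event lowers the value then measured by the stated amount.

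| Drop after a prior event | Forward events only | Prior events only | Either |
|---|---|---|---|
| 0 SD | 1.81 | 1.81 | 1.84 |
| 0.5 SD | 1.82 | 1.08 | 1.41 |
| 1.0 SD | 1.79 | 0.65 | 1.07 |
| 1.5 SD | 1.80 | 0.40 | 0.84 |

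Second simulation, 400,000 records, true odds ratio 1.5 per SD, varying the share of events that precede the sample. With no prior events the estimate is 1.51.

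| Prior share | 0.5 SD drop | 1 SD drop |
|---|---|---|
| 25% | 1.32 | 1.15 |
| 50% | 1.16 | 0.91 |
| 75% | 1.02 | 0.71 |

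Forward-only events recover the true value in every row of the first table. Including prior events attenuates the estimate whenever the event lowers the later value, and reverses it in some settings: the 1.5 SD row of the first table, and two of the six cells of the second, both with a 1 SD drop. The true odds ratio, the share and the drop are all assumed. Both simulations model one pattern, with risk rising with Anti-Xa and Anti-Xa falling after the event, which resembles bleeding. Thrombosis is not modelled.

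**The case against.** The strongest reply has four parts.

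- **Pooling is not explicit.** Section 2.10 gives a window and a metric; it does not say that prior and later events form one outcome variable. Outcome coding is commonly left to the analysis plan, which section 2.13 says will be finalised before database lock. For purely descriptive concordance, events on both sides of a sample may properly be listed. This stands as a limit: a single pooled outcome is the natural reading, not a stated rule. It does not remove the point, because the odds ratios and the predictive reading are attached to a two-sided window with no separation.
- **The claims are already restrained.** The Introduction says the study is not powered to rank assays by clinical endpoints, section 2.1 disclaims definitive prognostic performance, and section 2.16 allows regression only with enough events. With 66 patients and at most 132 samplings, assumed event rates of 2%, 5% or 10% per sampling give about 2.6, 6.6 or 13.2 events, so the model may never be fitted. This lowers the consequence but does not correct the time order.
- **Table 1 is an overview, and the case report form is not shown.** Section 4.1 mentions that adverse events are recorded, and section 4.2 that data come from the patient data management system. One therefore cannot conclude that forward events will go unrecorded. What stands is that neither section gives a window, and that the one event heading listed contradicts the outcome definition.
- **The look-back at sample 2 reaches some forward time.** True for gaps under 48 h, as the working shows.

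A reader might also infer that up to 48 h after sample 1 are lost. At a 72 h gap the look-back does begin at hour 48, but the protocol's forward window is 24 h, so at most 24 h of it is missed after sample 1.

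**Conclusion.** The concern holds in a limited form. The event window includes time before the sample, the result is read as predictive, and no section separates the periods. Table 1 conflicts with the outcome definition by listing only the look-back. The coverage limits (full at a 24 h gap, none from 48 h, none after sample 2) follow from the protocol's own schedule and from Table 1 as listed; the 12.5% figure also assumes uniform gaps.

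Odds ratios that include prior events could be attenuated or reversed. A reader might go further and infer that they will have the wrong sign, that most recorded events will precede the sample, or that the objective cannot be met at all. The documents support none of these. They contain no event rate, no split of events around the sample and no size of post-event change, and the aim is only a preliminary signal. Nor do they say that these odds ratios will shape a later trial: the remark in section 2.12 about informing future studies concerns the Anti-Xa and clotting-time association and its stratified analyses.

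Severity is low to moderate. This is the last of five exploratory outcomes, and the primary and secondary analyses are unaffected.

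**What to change.** 1. Reconcile exploratory outcome 5 with Table 1, so that both name the same windows.
2. For any odds ratio or statement about prediction, define the outcome as an event that starts within 24 h after the sample.
3. Add a look-forward event field for both samples, with date and time for bleeding, thrombosis and pulmonary embolism, filled from the patient data management system already used for data collection.
4. Report events in the 24 h before each sample separately, as a descriptor of the patient's state at sampling, and keep them out of the model's outcome.

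The cost is some wording and one set of fields drawn from existing records; no further blood sample, visit or patient is needed. It is easiest to do while data are still being collected. The downside is that fewer events count towards the outcome, so the analysis may stay descriptive, which sections 2.10 and 2.16 already allow.

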### Timeline

2.11

The study is planned to run over a total period of two years, with a recruitment phase lasting 12 months.

### Sample size

2.12

This study is designed to evaluate the association between Anti-Xa activity and VET variables, with a primary focus on CT in the RVV test, in critically ill patients receiving LMWH or UFH. The planned sample size allows estimation of this association under real-world ICU conditions and supports pre-specified mixed-effects modelling incorporating a limited number of biologically plausible effect modifiers. To account for heterogeneity in coagulation physiology, anticoagulant type (LMWH vs. UFH) and sepsis status will be examined as predefined effect modifiers within the modelling framework. These factors will not be treated as independently powered subgroups but will be analysed using interaction terms. The study is not powered for definitive detection of small correlation coefficients nor for confirmatory subgroup comparisons. Stratified analyses are therefore considered exploratory and hypothesis-generating. Findings will be interpreted cautiously and are intended to inform the design of future adequately powered multicentre studies.

The study is powered for estimation of the Anti-Xa–CT association. Analyses involving thrombin generation are predefined as secondary and exploratory. No separate formal sample size calculation was performed for TGA-CT correlations, as these analyses are hypothesis-generating. The sample size estimation was based on published data reporting a significant Spearman correlation for LMWH-treated patients between Anti-Xa levels and CT-RVV (*r* = 0.669, *p* = 0.0395) (34). For UFH, no exact coefficient was reported, although the same study demonstrated a clear association. For conservative planning, an effect size of *r* = 0.6 was assumed for UFH.

Calculations were performed with G*Power 3.1 (35) for a two-sided test of correlation (*α* = 0.05, power = 0.80). The required sample sizes were 19 independent observation pairs for *r* = 0.669 and 23 pairs for *r* = 0.6. As two temporally separated measurements are planned per patient, the non-independence of repeated measures was adjusted using a design effect with an intraclass correlation coefficient (ICC) of 0.3:

Design−Effect=1+(2−1)×0.3=1.3

$$\text{Effective observations}\;\mathrm{per}\;\text{patient}=\frac{2}{1.3}\approx 1.54$$

Thus, two correlated measurements correspond to approximately 1.54 independent observations. This results in approximately 13 LMWH-treated and 15 UFH-treated patients required to achieve the planned statistical power per anticoagulant category.

$$\mathrm{LMWH}:\frac{19}{1.54}\approx 13\;\text{patients}$$

$$\mathrm{UFH}:\frac{23}{1.54}\approx 15\;\text{patients}$$

Allowing for a 15% dropout rate and to ensure stable estimation within pre-specified mixed-effects models under heterogeneous ICU conditions, the target sample size was set to 30 LMWH-treated and 36 UFH-treated patients (total *n* = 66).

Sepsis status and other clinically relevant variables will be analysed as pre-specified effect modifiers within the mixed-effects framework rather than as separately powered subgroups.

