## Discussion

3

Anti-Xa activity remains the reference standard for monitoring heparin therapy but provides only a narrow perspective on anticoagulant effect. In critically ill patients, fixed dosing frequently results in sub- or supratherapeutic levels, and Anti-Xa values correlate poorly with clinical outcomes. Moreover, logistical barriers and delayed turnaround limit its feasibility as a routine monitoring tool in intensive care. Global assays such as the VET offer broader functional evaluation by integrating plasmatic and cellular components of coagulation. Experimental and volunteer studies demonstrated strong correlations between the VET clotting time and heparin concentration, and modified assays achieved high classification accuracy for therapeutic ranges. However, clinical data are inconsistent: some reports failed to show correlations beyond peak levels or at prophylactic dosing, and sensitivity varied considerably across devices and reagents. Similarly, TGA has shown promise at therapeutic LMWH concentrations but lacks standardization and is less reliable at lower doses. These limitations are particularly relevant in critical illness. Septic patients exhibit profound, dynamically evolving disturbances of haemostasis driven by inflammation, endothelial dysfunction, altered antithrombin levels, and consumption or dysregulation of pro- and anticoagulant pathways. These mechanisms result in substantial variability in heparin pharmacokinetics and pharmacodynamics, making fixed-dose anticoagulation particularly unreliable. In a larger cohort of critically ill COVID-19 patients with repeated paired measurements, CT-RVV showed only a weak-to-moderate correlation with Anti-Xa, highlighting that CT-based detection may be strongly context-dependent (17). This underscores the need to identify biological and methodological modifiers (e.g., inflammation, AT levels, factor consumption) that may explain discordant profiles. Anti-Xa quantifies circulating heparin activity but does not capture the global coagulation phenotype characteristic of sepsis, including heightened thrombin generation, impaired fibrinolysis, or parallel bleeding risk. VET may better reflect this complex state by integrating cellular and plasmatic contributions to clot formation. Although, VET also has clinically relevant limitations in the ICU: sensitivity to platelet dysfunction and mild fibrinolysis is assay- and device-dependent, and acute-phase changes (e.g., elevated fibrinogen) can increase clot firmness and partially mask anticoagulant effects. Nevertheless, these results may better reflect the overall state of the patient’s coagulation system. Therefore, VET is interpreted as a functional whole-blood phenotype that may complement—but not universally replace—concentration-based Anti-Xa monitoring. Understanding the relationship between Anti-Xa, VET, and global haemostatic markers in septic patients is therefore essential to determine whether Anti-Xa alone is sufficient or whether functional assays can identify under- or over-anticoagulation earlier. Given the high incidence of thromboembolic and bleeding complications in sepsis, this study’s findings are expected to directly inform individualized anticoagulation strategies and support more reliable monitoring pathways in this high-risk population.

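### The printed pair counts (19 and 23) do not follow from the stated correlation test, which gives 15 and 19: a minor reporting correction, in the safe direction, with no change in enrolment

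*Protocol article*

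**What the plan says.** Protocol article, section 2.12 (Sample size), builds the number in four steps.

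- **Effect sizes.** For LMWH it relies on "published data reporting a significant Spearman correlation for LMWH-treated patients between Anti-Xa levels and CT-RVV", r = 0.669 with p = 0.0395. For UFH: "For UFH, no exact coefficient was reported, although the same study demonstrated a clear association". It continues: "For conservative planning, an effect size of" r = 0.6 was assumed.
- **Pairs.** G*Power 3.1 was used "for a two-sided test of correlation", with alpha and power given as "0.05, power = 0.80". Then: "The required sample sizes were 19 independent observation pairs for" r = 0.669, and 23 for r = 0.6.
- **Patients.** Two samples per patient with an ICC of 0.3 give a design effect of 1.3 and 1.54 effective observations per patient, hence 13 LMWH and 15 UFH patients. The planned power per anticoagulant category is attached to these two numbers.
- **Target.** Citing 15% dropout and stable estimation in the mixed models, "the target sample size was set to 30 LMWH-treated and 36 UFH-treated patients", 66 in total.

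The Discussion (section 3) reports that in a larger cohort of critically ill COVID-19 patients with repeated pairs, "CT-RVV showed only a weak-to-moderate correlation with Anti-Xa". It gives no coefficient.

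**The concern.** Section 2.12 states every input needed to reproduce the pair counts, and a reader who enters them does not get 19 and 23. The 19 printed for r = 0.669 is the answer for r = 0.6. These counts are the only calculation behind the size of the study, and they are carried into the patient numbers.

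Two later steps leave the reader without what is needed. The move from 13 and 15 patients to 30 and 36 is larger than dropout explains, and the rest has a reason but no number. Calling r = 0.6 conservative also sits awkwardly beside the weaker correlation cited in the Discussion. The introduction plans to draw a conclusion from a weak correlation, so a reader needs to know which correlations this design can resolve.

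**Working it through.** **Inputs** (section 2.12 unless noted): two-sided test, alpha 0.05, power 0.80; r = 0.669 and 0.6; ICC 0.3; two samples per patient; 15% dropout; 30 and 36 patients. The range r = 0.3 to 0.4 is an assumption, since the Discussion gives no coefficient.

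**1. Pairs under the stated test** (exact bivariate-normal test of zero correlation)

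| r | pairs | power |
|---|---|---|
| 0.669 | 14 | 0.797 |
| 0.669 | **15** | 0.828 |
| 0.669 | 19 (printed) | 0.914 |
| 0.6 | 18 | 0.790 |
| 0.6 | **19** | 0.814 |
| 0.6 | 23 (printed) | 0.887 |

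Cross-check by Fisher z, n = ((1.960 + 0.842)/atanh r)² + 3:
- r = 0.669: (2.802/0.8089)² + 3 = 14.99.
- r = 0.6: (2.802/0.6931)² + 3 = 19.34, which rounds up to 20, one more than the exact test.

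**2. Could another setting give 19 and 23?**

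| Setting | r = 0.669 | r = 0.6 |
|---|---|---|
| One-sided, power 0.80 | 12 | 15 |
| Point-biserial model, power 0.80 | 12 | 17 |
| Exact, power 0.90 | 19 | 24 |
| Fisher z with Bonett–Wright Spearman variance (factor 1 + r²/2) | 17.68 → 18 | 22.28 → 23 |
| Spearman test, simulated (40,000 runs per n) | 16–17 | 20–22 |

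In the simulation the lower figure treats the planning r as a Spearman coefficient and the upper as a Pearson one. The figure of 20 has simulated power 0.797. At 15 and 19 pairs the Spearman test has about 78% power on the first reading. No setting tried returns both 19 and 23.

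**3. Patients.** Effective observations per patient = 2/1.3 = 1.54.
- Printed pairs: 19/1.54 = 12.35 → 13 and 23/1.54 = 14.95 → 15. This step reproduces.
- Pairs of 15 and 19: 9.75 → 10 and 12.35 → 13.

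**4. Dropout.** Dividing by 0.85: 13 → 15.3 → 16 and 15 → 17.6 → 18. Multiplying by 1.15: 14.95 → 15 and 17.25 → 18. Dropout therefore accounts for about 15–16 and 18 patients of the 30 and 36.

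**5. What 30 and 36 deliver**
- LMWH: 30 × 0.85 × 1.538 = 39.2 effective pairs.
- UFH: 36 × 0.85 × 1.538 = 47.1.
- Pooled: about 86.

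95% CI = tanh(atanh r ± 1.96 × √((1 + r²/2)/(n − 3))):
- LMWH, r = 0.669: standard error √(1.2238/36.2) = 0.184, interval 0.42 to 0.82.
- UFH, r = 0.6: standard error √(1.18/44.1) = 0.164, interval 0.36 to 0.77.

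Exact power at 39, 47 and 86 pairs:

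| true r | LMWH | UFH | pooled |
|---|---|---|---|
| 0.3 | 47% | 55% | 81% |
| 0.4 | 73% | 81% | 97% |
| planning value | >99% | >99% | – |

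Power reaches about 80% at r = 0.43 (LMWH) and 0.40 (UFH).

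**The case against.** The strongest reply is that nothing is lost. The printed pairs are too many, the target is larger again, and no analysis or decision depends on whether the first step said 15 or 19. That stands, and it is why this is a correction to stated figures and not a design fault.

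A second reply is that the planning coefficient and the outcome metric are Spearman, so 15 and 19 would be slightly too few. That also stands: the replacement must name its test. It does not rescue 19 and 23, which exceed the simulated Spearman requirement as well.

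Three stronger readings are tempting, and the document does not support them.

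- **That 66 patients are wrongly claimed to have 80% power, or that an unexplained doubling was applied.** The planned power is attached to 13 and 15 patients, not to 66. The target does equal twice 15 and twice 18, but only if dropout is applied by multiplying by 1.15; dividing by 0.85 gives 16 for LMWH, and twice 16 is 32. The text gives a reason beyond dropout, so the excess is unquantified, not unexplained.
- **That the Discussion refutes r = 0.6.** The word conservative is used for UFH only, relative to 0.669. The contrary cohort was of COVID-19 patients, is cited as showing context dependence, and comes without a coefficient.
- **That the study is underpowered.** The primary inference (section 2.13.1) is one mixed model over both drugs, and the drug-specific Spearman values are descriptive. Pooled power is about 81% even at r = 0.3. Section 2.12 also disclaims power for small correlations and calls stratified analyses exploratory.

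**Conclusion.** The pair counts are wrong as written. The stated test, alpha and power need 15 and 19 pairs, four fewer in each case, and the printed counts give about 91% and 89% power. Either the counts or the stated test or power must change; the document does not show which. At the assumed correlations the error is on the safe side and enrolment is unaffected, so this is a minor correction.

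What remains beyond the arithmetic is a request for clarity: what 30 and 36 patients deliver, and how far r = 0.6 can be called conservative. The delivered figures assume 15% dropout and take the plan's design effect of 1.3 as given. The pooled figures treat the primary analysis as a single correlation, which only approximates the mixed model.

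**What to change.** Reword section 2.12:

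1. Correct the pairs to 15 and 19, which gives 10 and 13 patients before dropout, or state the routine and power actually used. If Spearman is the planning metric, give Spearman-based counts (about 16–17 and 20–22).
2. State that 30 and 36 were set for precision, and report the result after dropout: about 39 and 47 effective pairs, 95% CI about 0.42–0.82 (LMWH, r = 0.669) and 0.36–0.77 (UFH, r = 0.6), and 80% power per drug for r of at least about 0.43 and 0.40.
3. Do not call r = 0.6 conservative without pointing to the weaker correlation cited in the Discussion. Add power at r = 0.3 and 0.4, per drug and pooled, labelled as an assumed range.

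The cost is a few sentences. The text will show openly that per-drug power is limited for weak correlations. Enrolment, sampling and analyses stay as they are.
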